**Research plan**

Study start date: September 2017

Duration of the study: 2 years

**Analysis**

Statistical analysis will be conducted with GraphPad Prism 5. The distribution of the variables will be evaluated with the Shapiro-Wilk test and parametric or non-parametric tests will be utilized accordingly. Pearson and Spearman tests will be conducted to assess the correlations between the different outcomes.

The significance level will be set at p<0.05.

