**Specifical objectives**

Main objective:

Assess the correlation between the STST performance and the distance walked during the 6MWT

Secondary objectives:

- Address the correlations between STST and 6MWT performances and the cardio-respiratory responses during both tests (heart rate HR; respiratory rate RR; pulsed oxygen saturation SpO2; blood pressure BP; dyspnea and leg fatigue)
- Address the correlations between both tests’ performances and; pulmonary function (forced vital capacity FVC; forced expiratory volume in 1s FEV1; peak expiratory flow PEF), respiratory muscle strength (maximal inspiratory and expiratory pressures MIP and MEP), quadriceps strength (QS) and health-related quality of life (HRQOL)
- Address the correlations between both tests’ performances and; anthropometric data (age, height, weight, body mass index BMI), hospitalizations and exacerbations within last year
- Question the specific insights of the STST in young children (from 6 to 10 years of age)
- Compare the cardio-respiratory responses between both similar tests (HR, RR, SpO2, BP, dyspnea and leg fatigue)
- Compare the cardio-respiratory responses between both different tests (HR, RR, SpO2, BP, dyspnea and leg fatigue)

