Confusion bias: This study is a randomized cross-over trial. Both tests will be conducted with the same subjects. In order to minimize the variation between subjects, 1 or 2 investigators maximum will conduct the tests in each center. The results of the first STST and 6MWT will not be communicated to the subjects before the second row to avoid any external influence.

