**Randomization procedure**

The randomization sequence will be computer-generated by a person not involved in the study using a random block size on a 1:1 ratio and will be sent to each of the CF Centers at the beginning of the study by the principal investigator (YC).

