All the children will complete the CFQ-R (Cystic Fibrosis Questionnaire). The French version of this scale has been validated [8]. 3 different questionnaires have been described: for children from 6 to 11 years, from 12 to 13 years and older than 14 years. All the procedures for the children and the investigators are precisely described within the scale completion document. The investigators will only have to help the children from 6 to 11 years by reading the questions and give examples whenever required. All the questions will be verbally answered by the children and answers will be reported on the questionnaire by the investigators. Two combinations are described for the different questions: « Très vrai / Vrai dans l’ensemble / Un peu vrai / Pas du tout vrai » and « Toujours / Souvent / parfois / Jamais ». A parental version of the questionnaire will be completed by the parents for the children younger than 14. Older children will complete the questionnaire on their own. The questionnaire will be filled in a quiet room.

Field tests realization:

Both field tests will be conducted twice. After the primary data collection, each test will be conducted once to account for the learning effect. The results of these first tests will not be transmitted to the children.

Both tests will then take place a second time. A 30-minute rest period will last between the habituation tests and the first field test and between both tests. The order of these tests will be randomized. HR, RR, BP, SpO2, dyspnea and leg fatigue will be measured before and after each test.

*STST*

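### The protocol randomises test order but plans a pooled correlation without it; a residual order effect would distort the primary STST-6MWT correlation, and adjusting for order costs one degree of freedom

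*Protocol*

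**What the plan says.** The validity section (paragraph on confusion bias) states the design: "This study is a randomized cross-over trial. Both tests will be conducted with the same subjects". The Randomization procedure allocates the order "using a random block size on a 1:1 ratio". Under Study procedures (field tests), each test is first run once for habituation and then both are run again; the text continues: "The order of these tests will be randomized". Thirty-minute rests separate the tests.

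The main objective under Specifical objectives is: "Assess the correlation between the STST performance and the distance walked during the 6MWT". A secondary objective is: "Compare the cardio-respiratory responses between both different tests". The variables are heart rate, respiratory rate, SpO2, blood pressure, dyspnea and leg fatigue.

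The Analysis section checks distributions with Shapiro-Wilk, after which "parametric or non-parametric tests will be utilized accordingly". For the correlations it adds: "Pearson and Spearman tests will be conducted to assess the correlations between the different outcomes". Neither this section nor any other part of the protocol mentions order, period or sequence as part of the analysis.

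**The concern.** Randomising the order makes half the children do the STST second and half do the 6MWT second. For a difference in means that is enough, because a period effect common to both tests cancels between the two orders. A correlation pooled over both orders behaves differently. Suppose each test suffers a little when it comes second. STST-first children then have lowered walking distances, and 6MWT-first children have lowered STST counts. Pooling the two groups adds variance to both scores and a negative component to their covariance. Neither has anything to do with whether the STST tracks functional capacity.

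The correlation is the primary result of a validity study, and the sample size leaves no spare power at r = 0.45. The distortion comes from a factor that the trial itself assigns, so it can be removed at almost no cost. In the paired comparisons the stake is smaller: extra residual variance.

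**Working it through.** **Inputs from the protocol.** r = 0.45, 80% power, alpha 0.05, 36 evaluable children, about 10% attrition, 40 enrolled (Sample size estimation); 1:1 orders (Randomization procedure). Sidedness is not stated; two-sided is assumed. The second attempt at each test is taken as the analysed value, since the first is for habituation.

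**The plan's own figure.** Fisher z: n = ((1.96 + 0.842)/atanh(0.45))² + 3 = 36.4, with power 79.5% at n = 36. The variant with a t critical value and small-sample bias term gives n = 36 (power 80.4%). One-sided testing would give 29.3, so the plan used two-sided. 36/0.9 = 40. The stated numbers reproduce.

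**Effect of order on the pooled correlation.** Let d1 and d2 be the drops in STST and 6MWT, in within-order SDs, when that test is done second. STST-first children have means (0, -d2) and 6MWT-first children (-d1, 0). With equal groups the between-order variances are d1²/4 and d2²/4, and the between-order covariance is -d1·d2/4. So

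pooled r = (0.45 - d1·d2/4) / sqrt((1 + d1²/4)(1 + d2²/4)).

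Example, d1 = d2 = 0.3: (0.45 - 0.0225)/1.0225 = 0.418. Power at n = 36 is Φ(atanh(r)·√33 - 1.96).

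| d1 | d2 | pooled r | power, n = 36 | n for 80% (unrounded) |
|---|---|---|---|---|
| 0 | 0 | 0.450 | 79.5% | 36.4 |
| 0.1 | 0.1 | 0.446 | 78.8% | 37.0 |
| 0.2 | 0.2 | 0.436 | 76.5% | 39.0 |
| 0.3 | 0.3 | 0.418 | 72.5% | 42.6 |
| 0.5 | 0.5 | 0.365 | 59.3% | 56.7 |
| 0.5 | 0 | 0.437 | 76.7% | 38.8 |
| 0.3 | -0.3 | 0.462 | 81.9% | 34.4 |
| 0.5 | -0.5 | 0.482 | 85.6% | 31.4 |

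The higher power in the last two rows is no benefit: there the correlation is overstated.

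**With order taken out.** A partial correlation given order keeps the target at 0.45 for any additive order effect. Its power is Φ(atanh(0.45)·√32 - 1.96) = 78.3%, against 79.5% for the pooled analysis when there is no order effect. The cost is 1.2 points.

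**Simulation check** (n = 36, 20,000 runs). At 0.5 SD on both tests: mean r 0.359 and power 60% unadjusted, 0.445 and 80% adjusted. With no order effect: power 81% unadjusted, 80% adjusted.

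**Paired comparisons.** A common period effect p (in SDs) leaves the mean STST-6MWT difference unbiased with balanced orders. It raises the variance of the difference from 2(1 - c) to 2(1 - c) + p², where c is the within-pair correlation, taken as 0.3 to 0.7. Lowest case, p = 0.2 and c = 0.3: sqrt(1.44/1.40) = 1.014. Highest, p = 0.5 and c = 0.7: sqrt(0.85/0.60) = 1.190. The standard error is therefore about 1-19% larger without a period term.

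**The case against.** Four objections deserve weight.

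- **The design already deals with order.** The habituation runs address learning, the 30-minute rests are meant to keep one test from affecting the next, and a one-minute STST may do little to a later walk. This stands as a reason to expect a small effect. At 0.1 SD on both tests adjustment gains nothing (78.3% against 78.8%); at 0.2 SD it gains about two points (78.3% against 76.5%). But nothing in the plan checks for or removes what remains.
- **A model term belongs in the SAP.** The SAP was not available and could add one, so it cannot be said that order will never be used. Still, the protocol is not silent: it names the correlation methods, and as named they leave out the factor that it randomises.
- **A paired test on balanced orders is acceptable.** True for bias under a common period effect; the gain from a period term is in precision.
- **A reader might infer more than the text supports.** One might conclude that any order effect lowers r; the table shows that one-sided effects barely move it and opposite effects raise it. One might conclude that pre-test values are ignored. Study procedures states "HR, RR, BP, SpO2, dyspnea and leg fatigue will be measured before and after each test", and the objectives speak of responses, so before-after changes are a natural reading that the Analysis section does not exclude. One might also conclude that the habituation order is left uncontrolled. The randomisation sentence follows the description of the second run, but the validity section speaks of randomised test order in general, and the flattened study diagram does not settle it.

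**Conclusion.** The point holds as a cheap improvement to the stated analysis, not as a demonstrated error. The protocol randomises order 1:1 and then names a pooled correlation that does not use it. A residual order effect would distort the primary correlation: downwards with same-direction effects on both tests (0.45 to between 0.436 and 0.365 for 0.2 to 0.5 SD), slightly with an effect on one test only, and upwards with opposite-sign effects. Every order-effect size here is an assumption, as are equal groups, additive effects and two-sided alpha.

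The sample size is not shown to be wrong; it reproduces. For the between-test comparisons the consequence is a standard error about 1-19% too large under a common period effect of 0.2 to 0.5 SD, with no bias in the mean difference. If the two tests were affected unequally on a common scale, the mean difference would shift by (d2 - d1)/2, and a period term would not remove that.

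**What to change.** In the Analysis section:

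1. Define the primary estimate as the partial Pearson (or partial Spearman) correlation between STST count and 6MWT distance given the randomised order. An equivalent route for Pearson is to subtract each order group's mean from both scores, correlate the residuals and test with N - 3 degrees of freedom (33 instead of 34 at N = 36). The unadjusted coefficient can be reported beside it.
2. For the paired STST-6MWT comparisons of cardio-respiratory responses, include a period term. In the parametric case this means averaging the two within-order mean differences and taking the error from within-order variation.

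The assigned order is known from the randomisation list, so no new measurement is needed; the order actually performed should be entered with the results. The cost is a few lines of text and one degree of freedom in each analysis. For the primary correlation that is about one power point if there is no order effect (79.5% to 78.3% at n = 36).

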**Stopping criteria**

All the investigators of this study are habituated to the conduction of such field tests and will consistently be watching over the children included in each Center. No side effects will be expected to occur.

The study procedure will be stopped if any exclusion criteria appears or upon request of the children.

**Data accessibility:**

The investigators will be the only person allowed to manipulate the data collected.

Children and their relatives will have access of their own data upon request at any time.

**Data conservation:**

All the data collected will be sent to [name], principal investigator, at the Le Havre Center after inclusion completion in each Center.

Data will be kept in a locked particular closet, inside the Le Havre Center.

**Final rapport:**

This study is aimed to be published in English in a peer-review journal indexed in MEDLINE/Pubmed.

